## Compliance with intervention procedures and use of the intervention

1. Which LEAP pages/modules/tools are used, how many times, for how long in total and on each occasion, and in what order?
2. To what extent do participants complete the activities and use all the tools within each module?
3. Is usage a personalised experience or are there patterns in usage across the sample?
4. What platform is used to access LEAP (PC, tablet and/or smartphone) and is the use of multiple platforms moderated by sociodemographic factors?
5. What percentage of participants opts to receive email notifications in the form of a weekly bulletin?
6. What percentage of participants responds to notifications? (i.e., logs in and updates personal information, recent behaviour, reviews goals etc.)
7. Which participants wear the pedometer for the duration of the trial and what is their pattern of usage?

## Compliance with intervention measurement procedures

1. What percentage of participants use the *Axivity* device according to protocol at baseline and post-intervention assessment?
2. What percentage of *Axivity* data is missing/incomplete or unreliable?
3. How many devices are lost at baseline and a follow-up assessment?
4. What percentage of participants completes the *24 hour recall diet* assessment at baseline and post-intervention assessment?
5. What percentage of the *24 hour recall* data is missing/incomplete or unreliable?
6. What percentage of participants completes the online *social* measures at baseline and post-intervention assessment?
7. What percentage of the online *social* measure data is missing/incomplete or unreliable?

## Validity of intervention measures and responsiveness to detect change

1. Is there preliminary data that suggests that the Axivity device is sensitive to detect change in all ambulatory behaviour in response to the intervention in this population?
2. Is there preliminary data that suggests that the 24 hour dietary recall measure is sensitive to detect change in response to the intervention in this population?
3. Is there preliminary data that suggests that the social measure is sensitive to detect change in response to the intervention in this population?

## Compliance with HAP battery measurement procedures

1. What is the mean (SD) length of time required to complete the full HAP assessment?
2. What percentage of participants completes the full HAP outcome assessment at each time point and how long does it take?
3. What percentage of outcome data is missing?

# Participant Recruitment

Primarily, individuals will be recruited through employers. We will work with Human Resource departments of medium to large businesses in the region (e.g. Nissan, Post Office, Local Authority, Department for Work and Pensions) and with Health Improvement Specialists ([name] and [name]), who have established relationships with local employers. We will aim to recruit individuals in full or part time work, and individuals who have recently retired (within the last 2 years). We cannot predict how easily we will access recently retired individuals via employers, therefore one of the aims of this pilot is to test this aspect of recruitment. If recruiting recently retired individuals is problematic, then we will adopt an additional recruitment strategy in the community. We will work with older people’s organisations (e.g. AgeUK, Gateshead Older People’s Forum and University of the Third Age) and advertise within local communities (e.g. supermarkets, Citizen Advice Bureau offices, libraries and community centre notice boards), with the aim to recruit individuals who have retired but not joined any national organisations, community or advocacy groups. Although we cannot predict who may be recruited via this strategy in the community, it increases the opportunity to include individuals in the trial who have experienced greater levels of disadvantage (e.g. through low incomes and poorer social networks) and who might, therefore, represent a key group of potential service users. Recruitment will begin in February and continue until April (3 months) unless recruitment targets (n=90) are met within a shorter timescale.

## Inclusion Criteria

A male or female who has retired in the last 2 years, is planning to retire in the next 2 years or who has reduced working hours in anticipation for retirement. The individual must own a PC, tablet or smartphone, and have reliable internet access at home, work or mobile 3G.

## Exclusion Criteria

Participants who cannot comprehend and speak fluent English will be excluded from participation. Similarly, participants will be excluded if they score ≥20 on the Center for Epidemiologic Studies Depression Scale (CESD), a measure of recent depressed feelings and behaviours, and/or scoring two or more standard deviations below the mean for age, gender, and education on the Paired Associate Learning (PAL), a measure of memory ability. Participants who are concerned about participating due to a health condition will be advised to consult their GP about their fitness and ability to participate: this also encompasses any participants with a probable severe mental health condition (as assessed by a brief telephone screening questionnaire). Volunteers with very high blood pressure (i.e. >180mmHg/>110) identified during the first heath assessment session will be advised to consult their GP as soon as possible; and discuss the potential benefit of taking part in this study. Volunteers who are concerned about participating due to a health condition will be advised to consult their GP about their fitness and ability to participate, and those advised not to participate will be excluded. Sampling

We will attempt to include participants who vary on the following criteria: retirement status; chronological age (younger vs older); gender; work category (manual, semiskilled or technical, managerial or professional), and work-related activity (physically demanding or sedentary). We will weight recruitment in favour of blue collar, manual and lower managerial occupations. To facilitate recruitment across these categories we will attempt to recruit employers who provide different forms of employment within the business (e.g. both office and blue collar positions), and if necessary, recruit employers that employ people in particular occupations if these are under-represented in our sample (e.g. high in work-related physical activity).

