## Recruitment and retention

1. What is the trial recruitment rate? (i.e., what percentage of people eligible to take part, in the specified geographical location, accepts the invitation to participate)?
2. What percentage of participants are recently retired compared to the percentage that are not yet retired?
3. Does the recruitment strategy result in the successful inclusion of participants from blue collar, manual or physical labour occupational backgrounds?
4. If the recruitment strategy via the community is adopted, in addition to the strategy via employers (see Section 5), then do the recruitment rate and the characteristics of the recruited sample differ for each strategy?
5. What is the trial retention rate? (i.e., what percentage of participants from each intervention arm remains in the trial at each follow-up assessment point?)

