# STUDY Procedure

This pilot trial will work through the following steps:

1. The trial administrator and (where appropriate) collaborating Health Improvement Specialists will contact Human Resources departments of local businesses to ask them if they would be willing to advertise the study to their employees or constituents (email, letters, posters in workplace etc) and where appropriate, contact individual employees or members of the organisation directly (e.g. personalised e-mail). If recruitment is also conducted in the community (e.g. in order to recruit people who have retired) then we will also contact community organisations of older adults and display posters in locations that may be frequented by people living in low socio economic neighbourhoods (more likely to have retired from blue collar or manual occupations rather than managerial or professional roles), and which aren’t linked specifically to existing membership or engagement with routine physical activity (e.g. sports centres). Our strategy therefore will be to display posters in low SES wards in Newcastle (e.g. Benwell, Elswick ) in the following locations: pubs; working men’s clubs; libraries; Citizen Advice Bureaus; supermarkets; noticeboards in religious buildings (e.g. churches, mosques) and shop windows.
2. Potential participants who are interested in participating will be asked to make contact with the trial administrator or to agree for the Human Resources department or community organisation to pass on their details to the research team who will then contact the potential participant directly.
3. The trial administrator will contact the Human Resources departments and community organisations in one week if there has not been any contact.
4. Over the telephone, a member of the research team will assess the potential participants for eligibility using the defined inclusion and exclusion criteria.
5. Eligible participants will be emailed or sent a study invitation letter, a participant information sheet and a consent form. They will be informed that one of the study team will make contact with them in the next five working days to discuss their participation in the study and to answer any questions.

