6. In the next five days, the trial administrator will telephone each eligible participant to answer any questions and to ascertain whether they would like to accept the invitation to participate. If there are any questions that can’t be answered over the phone by the administrator, a date for follow-up correspondence (either by e-mail or phone according to the preference of the potential participant) will be made. The administrator will request an answer to the question from the relevant trial team personnel, and will then relay this information to the participant during the arranged follow-up correspondence. On verbal consent, the trial administrator will ask that the participant sign the consent form and keep it until one of the research team visits them. The administrator will then schedule an appointment at a convenient time when one of the study team will visit the participant at their home or place of work to obtain the signed informed consent form and conduct the baseline assessment. The researcher will attend the appointment with spare consent forms in case the participant mislaid their original consent form.
7. Baseline assessment visit - after receiving informed consent, a member of the study team will administer the HAP battery assessment as per protocol (Appendix A). The activity monitor device will be attached to the participant, and it will be explained that the device is to be worn continuously for the next 7 days. The participant will be provided with a prepaid stamped address envelope to return the device after 7 days. The 24 hour recall dietary assessment tool procedure will be explained and participant will complete the first of three days to be recorded, and a web link to the social relationships tools will be provided. During this assessment session participants will be asked to provide information on smoking, alcohol consumption and demographic (Attachment 4 – Baseline data form).
8. The trial administrator will be informed by the member of the study team when baseline assessment is complete and the administrator will randomise the participant to one of the trial conditions recording key information (e.g. name, D.O.B. and assigned identification number) into a central database. A pedometer and instructions for its use will be posted to participants allocated to receive the LEAP intervention. The trial administrator will telephone or email the participant a few days later to check that the pedometer was received.

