a) Executive function. Verbal and category fluency tests will be used to assess participants’ executive function. Within a set timeframe, usually one minute per letter participants are instructed by the experimenter to speak aloud as many words as possible that begin with a specific letter (phonemic fluency) – this is repeated 3 times for 3 different letters (e.g., CFL or PRW). In a separate one minute window, participants are then instructed to speak aloud as many words as possible which belong to a specific category, such as animals (category fluency). Participants will be audio-recorded when performing these tasks, to allow for detailed analyses of the responses made, including total number of words, repetition and errors. Completion of these tests takes approximately 5 to 7 minutes.

b) Episodic memory. The paired associates learning (PAL) CANTAB test will be used. Boxes are displayed on a touchpad screen. The participant watches as the boxes are ‘opened’ automatically, one by one, in a randomised order. One or more of them will contain a pattern. The patterns are then displayed in the middle of the screen, one at a time, and the participant must touch the box where the pattern was originally located. If the participant makes an error, the patterns are re-presented to remind the participant of their locations. The difficulty level increases through the test. The number of patterns increases from one (with 7 empty boxes) to eight (with no empty boxes), which challenges even very able participants.

Test administration takes approximately 10 minutes, depending on level attained. The PAL has 21 outcome variables including errors made by the participant, the number of trials required to locate the pattern(s) correctly, memory scores and stages completed. These data are produced automatically.

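### Eligibility is settled by telephone, but the CES-D and PAL exclusions can be known only from the baseline battery, and no written step checks them before randomisation

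*Protocol*

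**What the plan says.** **Criteria.** Under Exclusion Criteria, "participants will be excluded if they score ≥20 on the Center for Epidemiologic Studies Depression Scale (CESD"), and/or on "scoring two or more standard deviations below the mean for age, gender, and education on the Paired Associate Learning (PAL"). The same section mentions a probable severe mental health condition, "as assessed by a brief telephone screening questionnaire". That questionnaire is not named, and it leads to advice to consult a GP, not to either score cut-off. Very high blood pressure found at the baseline session also leads to GP advice.

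**Telephone stage.** Study Procedure, step 4: "Over the telephone, a member of the research team will assess the potential participants for eligibility using the defined inclusion and exclusion criteria". Step 5 then calls these people eligible and sends them the invitation, information sheet and consent form. In step 6 they accept or decline.

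**Baseline and randomisation.** In step 7 the HAP battery is given after informed consent. In step 8 the trial administrator is told "when baseline assessment is complete and the administrator will randomise the participant to one of the trial conditions". Step 10 has the control link emailed straight after the baseline assessment.

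**Instruments.** Appendix A describes PAL as a CANTAB test on a touch screen, and CES-D as a questionnaire given through the online NIH Assessment Center. Neither is described anywhere else. On PAL it adds: "The PAL has 21 outcome variables including errors made by the participant, the number of trials required to locate the pattern(s) correctly"; the list goes on to memory scores and stages completed.

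**Feasibility output.** Recruitment question 1 asks "what percentage of people eligible to take part, in the specified geographical location, accepts the invitation to participate".

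**The concern.** Two of the stated exclusions cannot be applied at the point where the protocol says eligibility is decided. They become known only at the baseline visit, and the next numbered step triggers randomisation on completion of that visit, not on its results. A team following the steps faithfully could therefore randomise people whom the criteria exclude. The protocol also does not say how someone who fails at baseline is handled or counted.

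This matters more in a pilot than the small numbers suggest. The protocol gives the number of eligible people and the rates of recruitment and retention as reasons for running the trial. If *eligible* is fixed before two of the criteria have been measured, the loss between telephone screening and randomisation is not recorded. A definitive trial needs that figure to plan its recruitment effort.

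**Working it through.** **Order of events, from the numbered steps**

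| Step | What happens | CES-D and PAL known? |
|---|---|---|
| 4 | Eligibility decided by telephone on the defined criteria | No |
| 5–6 | People called eligible, invited; accept or decline | No |
| 7 | Consent received, then HAP battery given | Measured here |
| 8 | Administrator told baseline is complete; randomises | No comparison with the cut-offs stated |
| 10 | Control link sent straight after baseline | – |

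Step 4 cannot be carried out as written for PAL, because a touch-screen test cannot be given over the telephone. For CES-D, the only administration described is online within the baseline battery. The unnamed telephone questionnaire might conceivably include it, but the text ties that questionnaire to a different condition and a different consequence. Even if it did include CES-D, the PAL conflict would remain.

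**Effect on recruitment question 1.** Invitation and acceptance both fall in steps 5 and 6, so numerator and denominator are both on a telephone-eligible basis. The acceptance ratio is coherent as far as it goes. What it lacks is the next fraction, randomised over baseline-assessed.

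**Size.** The protocol gives no screen-failure figure to reproduce. The target of 90 is in the protocol (60 LEAP + 30 control = 90). The illustration rests on three assumptions:

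- PAL scores follow a normal distribution matching the norms, so P(Z ≤ −2) = 0.0228, and 90 × 0.0228 ≈ 2 people.
- A share *c* of telephone-eligible people score 20 or more on CES-D. The documents give no value, so a range is shown.
- The two failures are independent.

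Total failing: d = 1 − (1 − 0.0228)(1 − c). Expected number among 90: 90d. Baseline assessments needed for 90 randomised: 90/(1 − d), rounded up.

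| Assumed c | d | Of 90 | Assessments needed |
|---|---|---|---|
| 0% | 2.3% | 2.0 | 93 |
| 5% | 7.2% | 6.4 | 97 |
| 10% | 12.1% | 10.8 | 103 |
| 15% | 16.9% | 15.2 | 109 |
| 20% | 21.8% | 19.6 | 116 |

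Nearly all of the range comes from the assumed CES-D share. Only the first row is free of it.

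**The case against.** The best defence is that the protocol, read as a whole, implies a check. The criteria say that people with these scores will be excluded, Assessment Times puts baseline before randomisation, and the Randomisation section says that eligible participants are randomised. Appendix A has both instruments producing results automatically, so a check at the visit is feasible. The blood-pressure provision shows that the authors did not regard the telephone call as the last screen. In addition, the CONSORT diagram, the administrative flow chart and the separate HAP administration guidelines are not reproduced in the available text and could show such a check.

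This stands in part. The protocol makes a check possible and probably intends one, and the remedy is correspondingly small. But no numbered step contains it, the label *eligible* has already been given by step 5, and step 8 names completion of baseline as the trigger. A box in a flow chart would not remove the conflict between step 4 and Appendix A.

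Two stronger readings are tempting, and the documents do not support them.

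- **That the PAL rule picks out the best performers**, because fewer errors or trials lie below the mean. The criteria call PAL a measure of memory ability, and the list of outcome variables also includes memory scores and stages completed, where lower is worse. The poorer-memory side is plainly meant. What remains is that none of the 21 variables is named.
- **That retention would fall by 7–17 percentage points.** This requires ineligible people to be randomised and then removed, and no section prescribes such removal. Retention is defined by arm, so people excluded before step 8 never enter it.

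**Conclusion.** The concern holds as a sequencing conflict. Step 4 states a rule that cannot be carried out for PAL and has no described means of being carried out for CES-D. Step 8 states a trigger that bypasses both exclusions. As written, people who meet an exclusion criterion can be randomised, and the yield from telephone screening to randomisation is not captured.

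The size is modest and uncertain: about 2 of 90 from PAL alone under normality, and about 6 to 15 of 90 in total if 5–15% score 20 or more on CES-D, which is an assumption. The conflict in the text does not depend on these figures. It should be settled in the protocol itself, since eligibility and the order of randomisation are not matters for a statistical analysis plan.

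**What to change.** 1. Limit step 4 to the criteria that can be assessed by telephone.
2. Between steps 7 and 8, require CES-D and PAL to be completed and scored against the existing cut-offs. Reword step 8 so that randomisation follows confirmed eligibility, and bring step 10 into line.
3. Name the PAL variable used, and state that the exclusion applies on the poorer-memory side.
4. State that the 90 are those randomised.
5. Report acceptance among telephone-eligible people and, separately, the number screened out at baseline before randomisation.
6. Keep every randomised participant in the retention denominator. Restricting it to those later judged validly randomised would itself introduce a post-randomisation exclusion.
7. Reconcile where the GP-advice route falls relative to step 8. The passages need to agree; no new clinical rule is proposed, and no view is taken on the cut-offs.

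The cost is a few sentences and a short pre-randomisation checklist. Appendix A already has the scores generated automatically. Some extra baseline visits will be needed to reach 90 randomised (3 if only PAL failures occur, 7 to 19 under the assumed CES-D range), but the existing criteria already imply them.

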# Outcome Assessment

## Assessment Times

- Baseline before randomisation
- 2 months after starting the intervention.

## Baseline and 2-month Follow-up Assessments

The assessments at baseline and at 2-months are identical. The assessments will include behavioural measures of physical activity and inactivity, dietary intake and social relationships, and HAP measures. It is estimated that these measurements can be completed within 2 hours. The assessments will take place at the participant’s place of work. Participants who have retired will be asked to attend assessments at their previous place of work, at a local privately hired venue (e.g. community hall), or in their own homes. Assessments will be carried out by a member of the study team trained to administer the various measures. The psychological and social wellbeing questionnaires will be self-reported by the participant. In Appendix A there is the measurement battery protocol, including the list of measures, instructions for their administration and analysis of the data acquired).

# STUDY Procedure

This pilot trial will work through the following steps:

1. The trial administrator and (where appropriate) collaborating Health Improvement Specialists will contact Human Resources departments of local businesses to ask them if they would be willing to advertise the study to their employees or constituents (email, letters, posters in workplace etc) and where appropriate, contact individual employees or members of the organisation directly (e.g. personalised e-mail). If recruitment is also conducted in the community (e.g. in order to recruit people who have retired) then we will also contact community organisations of older adults and display posters in locations that may be frequented by people living in low socio economic neighbourhoods (more likely to have retired from blue collar or manual occupations rather than managerial or professional roles), and which aren’t linked specifically to existing membership or engagement with routine physical activity (e.g. sports centres). Our strategy therefore will be to display posters in low SES wards in Newcastle (e.g. Benwell, Elswick ) in the following locations: pubs; working men’s clubs; libraries; Citizen Advice Bureaus; supermarkets; noticeboards in religious buildings (e.g. churches, mosques) and shop windows.
2. Potential participants who are interested in participating will be asked to make contact with the trial administrator or to agree for the Human Resources department or community organisation to pass on their details to the research team who will then contact the potential participant directly.
3. The trial administrator will contact the Human Resources departments and community organisations in one week if there has not been any contact.
4. Over the telephone, a member of the research team will assess the potential participants for eligibility using the defined inclusion and exclusion criteria.
5. Eligible participants will be emailed or sent a study invitation letter, a participant information sheet and a consent form. They will be informed that one of the study team will make contact with them in the next five working days to discuss their participation in the study and to answer any questions.
6. In the next five days, the trial administrator will telephone each eligible participant to answer any questions and to ascertain whether they would like to accept the invitation to participate. If there are any questions that can’t be answered over the phone by the administrator, a date for follow-up correspondence (either by e-mail or phone according to the preference of the potential participant) will be made. The administrator will request an answer to the question from the relevant trial team personnel, and will then relay this information to the participant during the arranged follow-up correspondence. On verbal consent, the trial administrator will ask that the participant sign the consent form and keep it until one of the research team visits them. The administrator will then schedule an appointment at a convenient time when one of the study team will visit the participant at their home or place of work to obtain the signed informed consent form and conduct the baseline assessment. The researcher will attend the appointment with spare consent forms in case the participant mislaid their original consent form.
7. Baseline assessment visit - after receiving informed consent, a member of the study team will administer the HAP battery assessment as per protocol (Appendix A). The activity monitor device will be attached to the participant, and it will be explained that the device is to be worn continuously for the next 7 days. The participant will be provided with a prepaid stamped address envelope to return the device after 7 days. The 24 hour recall dietary assessment tool procedure will be explained and participant will complete the first of three days to be recorded, and a web link to the social relationships tools will be provided. During this assessment session participants will be asked to provide information on smoking, alcohol consumption and demographic (Attachment 4 – Baseline data form).
8. The trial administrator will be informed by the member of the study team when baseline assessment is complete and the administrator will randomise the participant to one of the trial conditions recording key information (e.g. name, D.O.B. and assigned identification number) into a central database. A pedometer and instructions for its use will be posted to participants allocated to receive the LEAP intervention. The trial administrator will telephone or email the participant a few days later to check that the pedometer was received.
9. Seven days after the trial administrator has confirmed that participants allocated to the LEAP intervention have received the pedometer, the trial administrator will email them a web link to access the intervention. They will also be provided with contact details of members of the study team to troubleshoot technical problems.
10. Immediately after the baseline assessment, the trial administrator will email a web link to the NHS LiveWell resource to participants allocated to receive the control intervention.
11. All participants will be reminded that they will be contacted again in approximately 6 weeks to arrange a follow-up visit by a member of the study team in two months’ time.
12. In the next three days, the trial administrator will telephone or email the participant to check that they received the web link to the intervention. During the call the administrator will arrange a date and time for a qualitative interview with those participants who have been identified as suitable using the purposive sampling procedure described in the qualitative protocol (see section 9). For participants randomised to the intervention group, the interview will be scheduled to take place no sooner than a week following the call to allow the participant to use the LEAP intervention and to ensure the interview is not conflated with use of LEAP. Approximately (n=6-8) appointments will be made with participants in the LEAP arm, and up to 4 appointments with participants in the control, with a further 6-8 and 4 appointments respectively being made toward the end of the trial. This will allow the research team to compare accounts of participation at the start and end of the trial respectively, potentially identifying unexpected participant expectations or disappointments/misunderstandings throughout the trial.
13. Six weeks after receiving the link to the LEAP or control intervention, the trial administrator will telephone participants to schedule an appointment at a convenient time in the next two weeks when one of the study team will visit the participant at their home or place of work to conduct the follow-up assessment. During the call the administrator will arrange a date and time for a qualitative interview with participants (n=6-8 in LEAP; n= 4 in control) who have been identified as suitable for a qualitative interview.
14. Two month follow-up assessment visit – the same procedure and protocols will be followed as were used for the baseline assessment. The members of the study team conducting the follow-up assessments will be blind to the trial condition of each participant.

The administrative steps for the pilot trial are represented in Figure 2.

[figure not shown]

